## Abstract

**Background:**

With the lack of effective therapy, chemoprevention, and vaccination against SARS-CoV-2, focusing on the immediate repurposing of existing drugs gives hope of curbing the COVID-19 pandemic. A recent unbiased genomics-guided tracing of the SARS-CoV-2 targets in human cells identified vitamin D among the three top-scoring molecules manifesting potential infection mitigation patterns. Growing pre-clinical and epidemiological observational data support this assumption. We hypothesized that vitamin D supplementation may improve the prognosis of COVID-19. The aim of this trial is to compare the effect of a single oral high dose of cholecalciferol versus a single oral standard dose on all-cause 14-day mortality rate in COVID-19 older adults at higher risk of worsening.

**Methods:**

The COVIT-TRIAL study is an open-label, multicenter, randomized controlled superiority trial. Patients aged ≥ 65 years with COVID-19 (diagnosed within the preceding 3 days with RT-PCR and/or chest CT scan) and at least one worsening risk factor at the time of inclusion (i.e., age ≥ 75 years, or SpO2 ≤ 94% in room air, or PaO2/FiO2 ≤ 300 mmHg), having no contraindications to vitamin D supplementation, and having received no vitamin D supplementation > 800 IU/day during the preceding month are recruited. Participants are randomized either to high-dose cholecalciferol (two 200,000 IU drinking vials at once on the day of inclusion) or to standard-dose cholecalciferol (one 50,000 IU drinking vial on the day of inclusion). Two hundred sixty participants are recruited and followed up for 28 days. The primary outcome measure is all-cause mortality within 14 days of inclusion. Secondary outcomes are the score changes on the World Health Organization Ordinal Scale for Clinical Improvement (OSCI) scale for COVID-19, and the between-group comparison of safety. These outcomes are assessed at baseline, day 14, and day 28, together with the serum concentrations of 25(OH)D, creatinine, calcium, and albumin at baseline and day 7.

**Discussion:**

COVIT-TRIAL is to our knowledge the first randomized controlled trial testing the effect of vitamin D supplementation on the prognosis of COVID-19 in high-risk older patients. High-dose vitamin D supplementation may be an effective, well-tolerated, and easily and immediately accessible treatment for COVID-19, the incidence of which increases dramatically and for which there are currently no scientifically validated treatments.

**Trial registration:**

ClinicalTrials.govNCT04344041. Registered on 14 April 2020

**Trial status:**

Recruiting. Recruitment is expected to be completed in April 2021.

## Background

Since December 2019, the COVID-19 caused by SARS-CoV-2 is spreading worldwide, affecting millions of people and leaving hundreds of thousands dead. With the lack of effective therapy, chemoprevention, and vaccination [1], focusing on the immediate repurposing of existing drugs gives hope of curbing the pandemic. Importantly, a recent unbiased genomics-guided tracing of the SARS-CoV-2 targets in human cells identified vitamin D among the three top-scoring molecules manifesting potential infection mitigation patterns through their effects on gene expression [2].

Vitamin D is a secosteroid hormone [3, 4]. By binding to the vitamin D response elements (VDRE) located in the promoter region of various genes, the expression of which is either activated or repressed, vitamin D may prevent COVID-19 adverse outcomes by regulating (i) the renin-angiotensin system (RAS), (ii) the innate and adaptive cellular immunity, (iii) the physical barriers, and (iv) the host frailty and comorbidities [5]. First, vitamin D reduces pulmonary permeability in animal models of acute respiratory distress syndrome (ARDS) by modulating the activity of RAS and the expression of the angiotensin-2 converting enzyme (ACE2) [6, 7]. This action is crucial since SARS-CoV-2 appears to use ACE2 as a receptor to infect host cells [8] and downregulates ACE2 expression [9]. ACE2 is expressed in many organs, including the endothelium and the pulmonary alveolar epithelial cells, where it has protective effects against inflammation. During COVID-19, downregulation of ACE2 results in an inflammatory chain reaction, the cytokine storm, complicated by ARDS [10, 11]. On the contrary, a study in rats with chemically induced ARDS showed that the administration of vitamin D increased the levels of mRNA and proteins ACE2 [12]. Rats supplemented with vitamin D had milder ARDS symptoms and moderate lung damage compared to controls. Second, many studies have described the antiviral effects of vitamin D, which works either by induction of antimicrobial peptides with direct antiviral activity against enveloped and non-enveloped viruses or by immunomodulatory and anti-inflammatory effects [13, 14]. These are potentially important during COVID-19 to limit the cytokine storm. Vitamin D can prevent ARDS [15] by reducing the production of pro-inflammatory Th1 cytokines, such as TNFα and interferon γ [13]. It also increases the expression of anti-inflammatory cytokines by macrophages [13]. Third, vitamin D stabilizes physical barriers [5]. These barriers are made up of closely linked cells to prevent outside agents (such as viruses) from reaching tissues susceptible to infection. Although viruses alter the integrity of the cell junction, vitamin D contributes to the maintenance of functional tight junctions via E-cadherin [5]. Fourth, the literature over the past decade on the non-skeletal effects of vitamin D has repeatedly reported that hypovitaminosis D is accompanied by various comorbidities including diabetes mellitus, hypertension, chronic cardiovascular and respiratory diseases, and cancers [3], all conditions that are associated with an increased risk of COVID-19 worsening and death.

Vitamin D is naturally synthesized by the skin during summer exposure to solar ultraviolet B rays. Hypovitaminosis D in humans is therefore more frequent in winter from October to March in the northern latitudes (above 20°) [3], which corresponds precisely to the latitudes where the highest fatality rates of COVID-19 were observed in the first winter months of 2020 [1]. In the past, coronaviruses and influenza viruses have shown a very strong seasonality, with preferential winter appearances in the northern hemisphere [16]. It should also be noted that the mortality of COVID-19 disproportionately affects BAME individuals (Blacks, Asians, and Ethnic Minorities) [17], whose higher cutaneous levels of melanin reduce the potential for cutaneous vitamin D synthesis.

The first reports indicated that cases with COVID-19 had, on average, 25(OH)D concentrations more than twice as low as controls without COVID-19 (respectively, 11.1 ng/mL versus 24.6 ng/mL, *P* = 0.004) [18]. Similarly, significant inverse correlations were found in 20 European countries between the mean serum 25(OH)D concentrations and the number of COVID-19 cases, as well as with mortality [19]. The severity of hypovitaminosis D appears to relate to the prognosis of COVID-19 since COVID-19 cases with hypovitaminosis D were more prone to experience severe COVID-19 (relative risk 1.59 with *P* = 0.02 if vitamin D insufficiency < 30 ng/mL) [20]. Finally, hypovitaminosis D was found to be associated with greater COVID-19 mortality risk (IRR = 1.56 with *P* < 0.001 if vitamin D deficiency; *P* = 0.404 after adjustment) [21]. These results support that enhancing serum 25(OH)D concentration may improve the prognosis of COVID-19, as strengthened by a pilot controlled trial reporting that the administration of calcifediol versus no calcifediol reduced the need for ICU treatment in 76 hospitalized participants with COVID-19 also receiving the best available therapy (mean age, 53 years; 40.8% women) [22]. Similarly, two quasi-experimental studies reported higher 14-day survival rates in frail older adults with COVID-19 receiving regular [23] and preferentially recent [24] vitamin D supplementation. Following these preliminary findings, larger interventional studies dedicated to COVID-19 are warranted for investigating the role of vitamin D supplementation on COVID-19 outcomes. Interestingly, previous meta-analyses revealed that high-dose prophylactic vitamin D supplementation was able to reduce the risk of respiratory tract infections [25, 26]. The optimal dose varied between 1000 and 4000 IU/day, suggesting the benefits of high-dose vitamin D supplementation, as did a previous study in an intensive care unit that reported a 17% mortality rate reduction in patients who received high-dose vitamin D compared to a placebo [27]. It is considered safe to take oral vitamin D supplements up to 10,000 IU/day for short periods [28], especially in older adults, a population predominantly affected by hypovitaminosis D and who should receive at least 1500 IU/day of vitamin D to get a desirable vitamin D status [3, 4].

We hypothesized that high-dose vitamin D supplementation could improve the prognosis of COVID-19.

## Methods

### Objectives

The primary objective is to compare the effect of a single oral high dose of cholecalciferol versus a single oral standard dose of cholecalciferol on 14-day all-cause mortality rate in older adults infected with SARS-CoV-2 at higher risk of worsening.

The secondary objectives of the study are as follows:
To compare the effect of high-dose versus standard-dose cholecalciferol on 28-day all-cause mortality rateTo compare the effect of high-dose versus standard-dose cholecalciferol on the clinical course of the disease (i.e., change of World Health Organization’s [WHO] Ordinal Scale for Clinical Improvement [OSCI] scale for COVID-19) within 14 and 28 days of inclusion [29]To compare the safety of high-dose versus standard-dose cholecalciferolTo compare the effect of high-dose versus standard-dose cholecalciferol on all-cause mortality rate and OSCI scale changes within 14 and 28 days of inclusion in the subgroup with vitamin D deficiency at baseline (i.e., serum 25(OH)D < 25 nmol/L)To determine the impact of serum 25(OH)D concentration at day 7 (i.e., serum 25(OH)D concentration < 75 nmol/L versus ≥ 75 nmol/L) on mortality rate and OSCI scale changes within 14 and 28 days of inclusionTo determine, in the subgroup with vitamin D deficiency at baseline (i.e., serum 25(OH)D < 25 nmol/L), the impact of the serum 25(OH)D concentration reached at day 7 (i.e., serum 25(OH)D concentration < 75 nmol/L versus ≥ 75 nmol/L) on mortality rate and OSCI scale changes within 14 and 28 days of inclusionTo model survival and clinical course (OSCI scale changes) within 14 and 28 days of inclusion according to the change of serum 25(OH)D concentration between day 0 and day 7To compare the mortality rates observed within 14 days of inclusion in each arm of the study with the mortality rates reported in the French hospital geriatric units receiving COVID-19 patients

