#### “Intervention” group

All participants receive the high-dose cholecalciferol (vitamin D_3_) supplement in a single oral intake on the day of inclusion (Mylan; 75008 Paris, France). Cholecalciferol is packaged in a drinking vial of 2 mL containing 200,000 IU. Thus, participants in the Intervention group take two vials at once, to reach the studied total dose of 400,000 IU. Vitamin D is ideally taken during food intakes because vitamin D is lipophilic and therefore better absorbed with fat. Such high dose is expected to quickly raise the serum 25(OH)D concentration above 75 nmol/L [30], which is not expected with lower doses [23]. This is all the more important in that, based on the knowledge of vitamin D non-skeletal effects, it appears that raising serum 25(OH)D concentrations above 75 nmol/L is necessary to obtain antiviral effect [4]. Finally, it has to be quoted that the chosen dose of 400,000 IU does not reach the dose of 500,000 IU that has been previously associated with side effects [31]. In addition, participants in the Intervention group will not take other vitamin D supplements for 45 days and will therefore receive the equivalent of a daily dose of 8900 IU/day over the period, less than the toxic dose of 10,000 IU/day [28].

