#### Analyses

The effect of high-dose vitamin D supplementation compared to standard-dose vitamin D supplementation will be determined using evaluation criteria, which are the mortality rates and the changes in OSCI score within 14 and 28 days of inclusion, using respectively the chi-square test or exact Fischer test, and independent samples *t* test or Mann-Whitney *U* test, as appropriate. An interim analysis of 100 participants is planned. It will focus on the primary outcome measure (i.e., all-cause mortality within 14 days of inclusion) with a *P* value of 0.001 used as the significance threshold for stopping the study. The final analysis of the primary outcome measure will use the *P* value of 0.0498 as the significance threshold (Peto-Haybittle method).

The proportions of participants with at least one serious adverse event within 28 days of inclusion will be compared using the chi-square test (or exact Fisher test if necessary). Survival curves will be plotted from baseline to day 28 using the Kaplan-Meier method, and a Cox proportional hazards model will be used to compare clinical outcomes between groups. The log-linearity assumptions will be checked for each quantitative variable introduced in the Cox models, and proportional hazards assumption will be checked for each variable to confirm adequacy for the Cox models.

Any exploratory analyses here will use multivariate logistic and proportional hazards regression. In addition, the stratification criterion for randomization will be also taken into account in the multivariate models. Excessive subgroup analyses can give rise to misleading results, and therefore, all subgroup investigations will be interpreted cautiously. In particular, subgroup analysis will be conducted depending on the severity of hypovitaminosis D at baseline and at day 7.

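### The planned comparison of arms within baseline 25(OH)D < 25 nmol/L is imprecise and has no stated contrast with other patients, so its P value cannot support a deficiency-specific claim

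*Protocol article*

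**What the plan says.** The Objectives section lists a comparison of the two doses "on all-cause mortality rate and OSCI scale changes within 14 and 28 days of inclusion in the subgroup with vitamin D deficiency at baseline", with the cut at 25 nmol/L. The Analyses section returns to this: "In particular, subgroup analysis will be conducted depending on the severity of hypovitaminosis D at baseline and at day 7". The tests it names are chi-square or Fisher for mortality, and t or Mann-Whitney for OSCI change. All of them compare arms. No comparison of the treatment effect between strata is stated.

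The same section carries a warning: "Excessive subgroup analyses can give rise to misleading results, and therefore, all subgroup investigations will be interpreted cautiously". It also opens a route to modelling: "Any exploratory analyses here will use multivariate logistic and proportional hazards regression".

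Baseline 25(OH)D is measured in all participants (Table 1; Blood sample collection procedures). It is not an eligibility limit and is not among the six minimisation criteria (Design). The sample size is set for the whole population only.

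**The concern.** A reader given a result for deficient patients will naturally ask whether high dose works differently in them. The stated tests cannot answer that. A significant P value below 25 nmol/L does not show a larger effect there, and a non-significant one does not show a smaller effect. Both follow largely from how many patients fall on each side of the cut.

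That number is not controlled. Recruitment runs from April 2020 to April 2021, and the Background says "Hypovitaminosis D in humans is therefore more frequent in winter from October to March", so the subgroup's size depends partly on when patients enter.

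The cut also fits the rationale loosely. The Intervention group section argues that "raising serum 25(OH)D concentrations above 75 nmol/L is necessary to obtain antiviral effect". Distance from 75 nmol/L is a graded quantity, and patients at 24 and 26 nmol/L have almost the same deficit.

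At stake is a subgroup statement, in either direction, that chance alone could produce.

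**Working it through.** **Inputs from the Sample size calculation section.** 14-day mortality of 20% v 8% (12 points), two-sided alpha 5%, power 80%, 125 evaluable and 130 recruited per arm.

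**Assumed input.** The share below 25 nmol/L is not in the document. The only level that bears on it is a mean of 11.1 ng/mL in COVID-19 cases in one report cited in the Background, or 11.1 × 2.5 ≈ 28 nmol/L. I take 20% to 45%.

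**Step 1: the plan's own figure.** With unpooled variance, n = (1.96 + 0.8416)² × (0.20×0.80 + 0.08×0.92) / 0.12² = 7.849 × 0.2336 / 0.0144 ≈ 127. The arcsine method gives about 125. The stated 125 per group is reproduced.

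**Step 2: power in each stratum.** Exact enumeration of the uncorrected chi-square test, 20% v 8% in both strata, 130 per arm split by share:

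| Share < 25 nmol/L | n per arm, deficient / rest | Expected deaths, deficient (both arms) | Power, deficient (a) | Power, rest (b) |
|---|---|---|---|---|
| 20% | 26 / 104 | 7 | 25% | 72% |
| 30% | 39 / 91 | 11 | 35% | 66% |
| 45% | 58 / 72 | 16 | 47% | 56% |

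Expected deaths are n × (0.20 + 0.08). The 95% interval half-width for the risk difference is 1.96 × √(0.2336/n): about 19 points at n = 26 and 12 points at n = 58.

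**Step 3: discordant results when the true effect is identical.** The strata are independent. Deficient alone significant = a(1 − b). Rest alone significant = b(1 − a).

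| Share | Deficient alone | Rest alone | Exactly one |
|---|---|---|---|
| 20% | 0.250 × 0.277 = 7% | 0.723 × 0.750 = 54% | 61% |
| 30% | 0.347 × 0.341 = 12% | 0.659 × 0.653 = 43% | 55% |
| 45% | 0.471 × 0.443 = 21% | 0.557 × 0.529 = 29% | 50% |

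With 125 evaluable per arm instead of 130, the last column is 61%, 54% and 50%. With no effect in either stratum, the deficient stratum alone is significant in about 5% of trials.

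**Step 4: power of the interaction.** Binary version, 250 evaluable, benefit of 12 points in the deficient and 0 in the rest. SE = √(0.2336/n₁ + 0.32/n₂), power = Φ(0.12/SE − 1.96).
- Share 20% (n₁ = 25, n₂ = 100): SE = 0.112, power 19%.
- Share 30%: 23%. Share 40%: about 25%.
- Share 50% (62.5 each): SE = 0.094, power 25%.

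**The case against.** The strongest reply is that the protocol never asks whether the effect differs by vitamin D status. It asks for the effect in deficient patients, and a randomised comparison within them estimates that. This stands: a reader might infer that the objective cannot be answered, and that is not so. It can be answered, with a wide interval.

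A reader might also infer that the plan looks only below 25 nmol/L. It does not, since the Analyses section plans that "subgroup analysis will be conducted depending on the severity of hypovitaminosis D at baseline".

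A third tempting reading takes 50% to 61% as the risk of a false deficiency-specific benefit. Most of that figure is the reverse pattern. The deficient-alone pattern is 7% to 21%, and the whole calculation applies only if the remaining patients are tested too.

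Other points also carry weight. The absence of 25(OH)D from entry limits and minimisation does not bias the comparison. It affects only subgroup size and chance balance. Exclusion of patients supplemented above 800 IU/day pushes entry towards low levels, so the subgroup may be larger than assumed, though at a 60% share power is still only about 56%. Misclassification near a cut from assay error is common to any threshold, and the same error would blur a continuous modifier. An analysis plan not shown here may contain an interaction test, so its absence from the article is not itself the finding.

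The warning about cautious interpretation is real and limits the harm. But caution supplies no contrast that separates a chance pattern from a true difference, and the objective as worded still puts the result on a within-subgroup test.

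**Conclusion.** The point holds in a limited form. The comparison below 25 nmol/L is a legitimate but imprecise estimate: power is about 25% to 47% for the full design effect, with an interval of roughly ±19 to ±12 points. Its P value says nothing about whether deficient patients respond differently. Under one common effect, with both strata tested, exactly one is significant in about 50% to 61% of trials, more often the non-deficient stratum.

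These figures rest on an assumed share of 20% to 45% and on the design rates of 20% and 8% applying in both strata. The primary analysis is not affected.

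**What to change.** Reword the objective and the matching sentence in Analyses:

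- Pre-specify, as exploratory, one treatment-by-baseline-25(OH)D interaction for 14-day mortality, with 25(OH)D continuous. Fit it in all randomised patients with a baseline value, using the logistic regression the Analyses section already allows.
- Show the estimated treatment effect with confidence intervals across baseline levels, for example at 25, 50 and 75 nmol/L.
- Keep the < 25 nmol/L result as a descriptive estimate with its interval.
- Base any statement about a deficiency-specific effect on the interaction.

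The cost is the wording of one objective and one analysis sentence. No new data are needed. The interaction is itself weak at this sample size (about 19% to 25% power for 12 points v 0 in a binary version), and the text should say so. The gain is the right contrast with an honest interval, not more power.

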### Design

This is an open-label, multicenter, randomized, controlled, parallel group, intent-to-treat, superiority clinical trial. Figure 1 illustrates the trial design, and Table 1 summarizes the timing of the trial. All participants receive the intervention in a single oral intake on the day of inclusion. Treatment allocation is carried out according to a 1:1 ratio by means of dynamic randomization (randomization by minimization) taking into account 6 criteria: worsening risk factor (age ≥ 75 years, or oxygen dependence characterized by a peripheral capillary oxygen saturation [SpO2] ≤ 94% in room air, or ratio of partial oxygen pressure [PaO2] to oxygen fraction in the inspired air [FiO2] ≤ 300 mmHg), criterion used for COVID-19 diagnosis (RT-PCR or chest CT scan), hospitalization (yes/no), concomitant use of anti-infective drugs such as hydroxychloroquine or azithromycin among others, concomitant use of corticosteroids, and recruiting center. This dynamic randomization is established by the Department of Biostatistics and Methodology of the University Hospital of Angers, France. Randomization is performed using a web-based system (Ennov Clinical®).

**Fig. 1 Fig1:**
[figure not shown]
Trial flow chart

**Table 1 Tab1:** Calendar summary

	Study period			
	Enrolment and allocation	Post-allocation		Close-out
Timepoint	Day 0	Day 7 (± 1 day)	Day 14	Day 28
**Enrolment**				
Eligibility screen	X			
Inclusion (written consent or emergency inclusion procedure)	X			
Allocation	X			
**Interventions**				
High-dose vitamin D supplementation	X			
Standard-dose vitamin D supplementation	X			
**Assessments**				
Socio-demographic, clinical, treatment data	X		X	X
Blood test for serum 25(OH)D, creatinine, calcium, and albumin	X	X		
OSCI scale	X		X	X
AE/SAE		X	X	X
All-cause death		X	X	X

Treatments were transmitted to the central pharmacy of Angers University Hospital, which is in charge of shipping the treatments to each recruiting center taking into account the pace of inclusion within each center. Study medication packs are identified by means of random numbers. The Ennov Clinical® software assigned to the patient a study medication pack (random number) corresponding to the result of the dynamic randomization.

